## 6. STUDY POPULATION

### a. INCLUSION CRITERIA

- 1) Children and adolescents aged 0 to 18 who have tested SARS-CoV-2 positive (PCR or Rapid Antigen Tests) or influenza (PCR or Rapid Antigen Tests) in the previous 3 months are eligible for enrollment.

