| Inclusion Criteria:         | Children and adolescents aged 0 to 18 who have tested SARS-CoV-2 positive (PCR or Rapid Antigen Tests) or influenza (PCR or Rapid Antigen Tests) in the previous 2 months are eligible for enrollment.                                                                                                                                                                                                                                                                                                                                                                                                                                                                                                                                                                                                                                                                                                                                                                                                                                                                                                                                                                                                                                                                                                                                                                                                                                                                                                                                                                                                                                                                                                                                                                          |

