Follow-up studies on MIS-C indicate that the majority of patients recover fully, including improvement of cardiac dysfunction. Some have suggested that PCC in children is a subclinical presentation of MIS-C. However, elevated markers of inflammation, a central feature of MIS-C, are uncommon in long COVID. Furthermore, there is limited evidence that immunomodulatory treatment, which is very effective in managing MIS-C, has a role in treating long COVID. There are some studies on low-dose naltrexone (LDN) that suggest some patients experience fewer number of symptoms, and improved clinical symptoms, however randomised placebo controlled trials are required. LDN can act as an immunomodulator in multiple autoimmune diseases and malignant tumors. Given the distinct differences between children and adults with COVID-19 infection, paediatric-specific research on PCC is essential.

In September 2022, a panel of 27 experts convened to establish a clinical case definition for the post-COVID-19 condition in children and adolescents, informed by the scientific data available at that time. This definition is expected to undergo revisions as further high-quality evidence emerges and our collective understanding of the condition deepens. The World Health Organization (WHO) defines PCC, as:

- Occurring in individuals with a history of confirmed or probable SARS-CoV-2 infection
- Symptoms last at least 2 months, initially occurring within 3 months of acute COVID-19
- Symptoms generally impact everyday functioning, such as changes in eating habits, physical activity, behaviour, academic performance, social functions (interactions with friends, peers, and family) and developmental milestones.
- Symptoms may be new onset following initial recovery from an acute COVID-19 episode or persist from the initial illness.
- They may also fluctuate or relapse over time.
- Workup may reveal additional diagnoses, but this does not exclude the diagnosis of post-COVID-19 condition.
- More frequently reported symptoms in children compared with controls are fatigue, altered smell/anosmia and anxiety. Other symptoms have also been reported.
- This definition can be applied to children of all ages, with age-specific symptoms and impact on everyday function considered.

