### c. OUTCOME MEASURES

#### **Primary**

1. Cumulative incidence of PCC at 3 months in children who tested COVID-19 positive (PCR, or RAT), and the proportion with PCC at 6 and 12 months post-infection will be assessed from survey responses and follow-up.

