#### Data from consented participants

Following consent, survey data will be collected from those enrolled using an online RedCap baseline questionnaire to be completed at recruitment, followed by questionnaires at 3, 6, and 12 months post-infection. The WCHN study team will validate the positive test results of consented participants with CDCB. Questionnaires will be available for parents/carers or participants to answer where applicable. Quality of life questions will be available in two of the fastest-growing non-English languages used at home in South Australia: Mandarin, and Vietnamese. The survey is based on the International Severe Acute Respiratory and Emerging Infection Consortium (ISARIC) COVID-19 Paediatric follow-up protocol and questionnaire. If there is no response from a survey after one week, 2 reminders will be sent a week apart. Data will be collected using a secure password-protected web application housed on a SA Health data server (RedCap).

Data to be collected includes:

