#### **Baseline data (1 month after swab result or hospital discharge)**

- Name of person filling in the questionnaire and relationship with the case.
- Sex/gender

- Ethnicity
- Medically diagnosed conditions prior to respiratory infection
- Symptoms of acute COVID-19 infection (first 14 days)
- History of confirmed SARS-CoV-2 tests

Collected by study staff:

- Vaccination history (confirmed on the Australian Immunisation Register)
- If hospitalised (from EMR):
  - Length of stay
  - Number of viral infections
  - Treatment, e.g., antivirals, antibodies
  - Pneumonia Y/N
  - ICU/HDU admission Y/N
  - Respiratory support Y/N

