## PARTICIPANT RECRUITMENT

### c. RECRUITMENT PROCEDURE

**Phase 1 WCH:** Each fortnight, parents of children aged 0 to 18 will be contacted if their child is identified as having a positive PCR or Rapid Antigen Test (RAT) for COVID-19 or influenza infection at the WCHN. They will be sent one phone text message informing them about the study and inviting them to participate using an online link. The link will take them to the online information sheet and consent for the study.

Before contacting the parents of WCHN hospitalised children, the electronic medical record will be checked to ensure no alerts are present.

**Phase 2 SA Health Notifications:** SA Health receive notifications of SARS-CoV-2 PCR. They also receive notification of influenza PCR-positive cases. Every month, the Disease Surveillance and Investigation Section team (CDCB) collates these notifications for COVID-19 and influenza. A list of children who have accessed the statewide WCHN palliative care service will be cross-matched with influenza and COVID-19 notifications. Influenza and COVID-19 notifications with a matching date of birth will be excluded from receiving an invitation. After data validation, an SMS will be sent to the mobile phone number of the cases. The SMS will contain a link to the information sheet and consent form, securely stored on a RedCap database housed on the CALHN server. SA Health notification data does not specify the relationship between the contact mobile number entered in the online reporting system, to the case. However, there will be wording that ensures it is clear that a parent or guardian is required to consent to the study. This recruitment method will replace invites from phase 1 (WCHN) once governance approval is provided to avoid duplication of invites.

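### The only inclusion criterion gives two enrolment windows, 2 months and 3 months, and the longer one allows consent and baseline to fall at the primary outcome time point.

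*Protocol*

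**What the plan says.** The synopsis, under Inclusion Criteria, admits children with a positive SARS-CoV-2 or influenza test "in the previous 2 months are eligible for enrollment". Section 6.a repeats the criterion with a different limit: "in the previous 3 months are eligible for enrollment". It is the only inclusion criterion.

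Four other statements fix the timeline around it:

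- Section 5.c heads the first survey "Baseline data (1 month after swab result or hospital discharge". That survey asks about symptoms in the first 14 days and about conditions diagnosed before the infection.
- Follow-up is counted from infection, not from enrolment: the baseline questionnaire is completed at recruitment, "followed by questionnaires at 3, 6, and 12 months post-infection".
- The primary outcome in Section 4.c is "Cumulative incidence of PCC at 3 months in children who tested COVID-19 positive".
- The WHO case definition cited in Section 3.c includes: "Symptoms last at least 2 months, initially occurring within 3 months of acute COVID-19".

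**The concern.** A child swabbed ten weeks ago is eligible under Section 6.a and ineligible under the synopsis. A statistical analysis plan cannot settle who may be enrolled, so the protocol has to.

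The longer window also raises a design problem. Enrolment is meant to come before the outcome, but a 3-month window ends where the primary outcome is measured. A family consenting late in that window will often know whether symptoms have persisted. If families of affected children are more willing to join, the estimated incidence of PCC, and of PAS after influenza, reflects that willingness as well as the risk. For these late enrolees, self-reported baseline items would be recalled at about the time the outcome is reported. The 3-month survey, which asks about events since the previous survey, would then cover only days or weeks.

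**Working it through.** **1. Timeline, from the protocol's own time points (months after the positive test).**

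| Event | Synopsis window | Section 6.a window |
|---|---|---|
| Planned baseline (swab-based) | 1 | 1 |
| Earliest point at which symptoms present since the acute illness have lasted 2 months | 2 | 2 |
| Latest consent, hence latest start of baseline | 2 | 3 |
| Primary outcome | 3 | 3 |
| Shortest gap from consent to outcome | 3 − 2 = 1 | 3 − 3 = 0 |

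Under Section 6.a, the whole of month 3 is open for enrolment after the duration criterion can already have been met. Under the synopsis, enrolment closes at that point.

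**2. How late could consent be?** Invitations are sent on a fortnightly cycle in phase 1 ("Each fortnight, parents of children aged 0 to 18 will be contacted") and after monthly collation and data validation in phase 2 (Section 6.c). No section limits the time from invitation to consent except the eligibility window itself. The share consenting in month 3 is therefore not known.

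**3. The plan's own precision, as a yardstick.** Table 2 gives a margin of 1.06 points at 3% incidence and n = 1,000. Check: 1.96 × √(0.03 × 0.97 / 1,000) = 1.06 points. It reproduces as a half-width. With 1,222 cases and 20% loss, n = 978 and the half-width is 1.07 points.

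**4. Illustration of selection.** Let p be the true incidence, f the share of participants who consent in month 3, and r the ratio of participation in affected to unaffected families in that month. Selection before month 3 is set to zero.

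Estimated incidence = (1 − f) × p + f × rp / (rp + 1 − p)

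Only p = 3% has a basis in the protocol (the middle column of Table 2). **f and r are assumptions.** The incidence among month-3 consenters is 4.43% for r = 1.5, 5.83% for r = 2 (0.06 / 1.03) and 8.49% for r = 3 (0.09 / 1.06).

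| f | r = 1.5 | r = 2 | r = 3 |
|---|---|---|---|
| 10% | 3.14% | 3.28% | 3.55% |
| 25% | 3.36% | 3.71% | 4.37% |
| 33% | 3.47% | 3.93% | 4.81% |

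For the bias to reach the 1.06-point margin, f must be about 1.06 / 5.49 = 19% at r = 3, about 1.06 / 2.83 = 37% at r = 2, and about 1.06 / 1.43 = 74% at r = 1.5. Within the table, only r = 3 with f of 25% or 33% exceeds the margin.

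**5. Could it be checked afterwards?** Hardly, in phase 2. Section 5.c says the study team receives only aggregated counts of invitations sent, so individual responders and non-responders cannot be compared.

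**The case against.** The strongest reply is that late consent may be uncommon. Phase 1 sends a single text message on a two-week cycle, phase 2 works monthly, and the reminders in Section 5.c are for surveys, not for the invitation. A family consenting in month 3 would usually have left one message unanswered for a month or more, although the validation delay in phase 2 is not stated. This stands, and it is why the bias can only be called possible.

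Two stronger readings are tempting and are not supported.

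- A reader might infer that the primary incidence is inflated by up to 1.81 points (4.81% against 3%). That needs a third of participants, about 403 of 1,222, to consent in month 3 with a threefold difference in participation. Neither figure has a source in the protocol. Even the upward direction is only probable: a shortened recall period in the 3-month survey could work the other way.
- A reader might infer that the prediction model for Objective 3 no longer predicts forward in time. The predictors named in Section 8.c are age, sex, pre-existing conditions and socioeconomic status, and three of these hardly depend on recall. Vaccination is taken from the immunisation register and hospital data from the medical record. The difficulty is confined to late enrolees and to self-reported items: prior conditions and, if used, acute symptoms.

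It is also fair to say that the outcome is not always settled by month 3, since the cited definition allows onset up to 3 months. Conversely, families who consent in month 2 may also know that symptoms are persisting, so a 2-month limit reduces symptom-driven consent without removing it. None of this resolves the contradiction between the two windows.

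**Conclusion.** The contradiction is certain and rests on no assumption: the same criterion carries two limits in current text. That the 3-month version conflicts with a 1-month baseline and permits consent with no time left before the primary outcome also follows directly from the stated time points.

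That consent could depend on the outcome, and that PCC and PAS incidence could be biased, probably upwards, is a reasonable consequence of unknown size. It depends on the share consenting in month 3 and on how strongly symptoms drive participation, and the protocol gives neither. The illustration shows only that the effect could range from negligible to larger than the planned margin of error. The text must be reconciled; no quantified bias should be attached to the finding.

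**What to change.** State one window in the synopsis and in Section 6.a, no longer than 2 months from swab, and bring the baseline heading in Section 5.c into line with it. Require the baseline survey to be completed before the 3-month survey opens, enforced by a REDCap date check. The existing survey reminders, at one and two weeks, fit within the one-month gap this leaves.

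Keep any children already enrolled at 2 to 3 months, since they were eligible under Section 6.a and Section 8.c lets participants contribute wherever follow-up is available. Add a sensitivity analysis of the primary incidence, the relative risk and the prediction model by swab-to-consent interval, with and without these children.

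The cost is a short amendment, a database check and one additional analysis. Some late responders become ineligible, and symptom-driven consent is reduced but not removed.

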### b. EXCLUSION CRITERIA

- 1) Inability to give informed consent
- 2) No mobile phone number
- 3) Children and adolescents who are under the care of the statewide WCHN Palliative care service

## PARTICIPANT RECRUITMENT

### c. RECRUITMENT PROCEDURE

**Phase 1 WCH:** Each fortnight, parents of children aged 0 to 18 will be contacted if their child is identified as having a positive PCR or Rapid Antigen Test (RAT) for COVID-19 or influenza infection at the WCHN. They will be sent one phone text message informing them about the study and inviting them to participate using an online link. The link will take them to the online information sheet and consent for the study.

Before contacting the parents of WCHN hospitalised children, the electronic medical record will be checked to ensure no alerts are present.

**Phase 2 SA Health Notifications:** SA Health receive notifications of SARS-CoV-2 PCR. They also receive notification of influenza PCR-positive cases. Every month, the Disease Surveillance and Investigation Section team (CDCB) collates these notifications for COVID-19 and influenza. A list of children who have accessed the statewide WCHN palliative care service will be cross-matched with influenza and COVID-19 notifications. Influenza and COVID-19 notifications with a matching date of birth will be excluded from receiving an invitation. After data validation, an SMS will be sent to the mobile phone number of the cases. The SMS will contain a link to the information sheet and consent form, securely stored on a RedCap database housed on the CALHN server. SA Health notification data does not specify the relationship between the contact mobile number entered in the online reporting system, to the case. However, there will be wording that ensures it is clear that a parent or guardian is required to consent to the study. This recruitment method will replace invites from phase 1 (WCHN) once governance approval is provided to avoid duplication of invites.

### d. CONSENT

During phase 1 of recruitment a waiver of consent will be used to gather and report basic baseline clinical information of all COVID-19 and influenza cases that were swabbed at a WCHN site. A waiver is already in place for all WCHN COVID-19 and influenza cases through the PAEDS study.

The participant information sheet and electronic consent will be accessible on the RedCap survey. The online consent will require an online signature of the parent and an online assent signature of their 12-18-year-old if they are also filling out the survey. A paper consent will be able to be provided upon request, but it will be the exception.

## 7. PARTICIPANT SAFETY AND WITHDRAWAL

### a. RISK MANAGEMENT AND SAFETY

Whilst there are fewer risks than in interventional studies, some risks are described below with the mitigation strategies the study will use.

- 1) Psychological or Emotional Impact: The wellbeing questions may prompt emotions among participants and parents. The questionnaires are validated for children, adolescents, and their parents. Measures have been taken to minimise the risk of distress. Refer to Appendix A 'Distress Protocol'.
- 2) Privacy and Confidentiality: The data will be collected using a password-protected RedCap database stored on an SA Health server behind an SA Health firewall. The database will only be able to be accessed by designated study staff, who are employees of SA Health. Identifiable data obtained from WCHN eligible cases will not be provided to non-WCH members of the study team without the participant's consent. Data will only be able to be extracted by the study PI, and no identifiable data will be stored outside of the password-protected RedCap database. The final dataset will be de-identified before being stored securely on a SA Health computer, only accessible to study staff. Information published from this study will not identify any participants involved in this study.
- 3) Economic Implications: It is expected that the survey will take approximately 10-15 minutes to complete. Efforts have been made to ensure that only necessary information is collected. Despite only having a small time requirement, it is still a burden in what can be busy family schedules. We have tried to ensure that the online platform remains flexible and that participants are compensated for their participation at \$10 for each completed survey (\$40 in total).
- 4) Coercion: The information sheet and consent form will clarify that participation is strictly voluntary and not linked to institutional benefits or repercussions. The reimbursement is modest, ensuring that the reimbursement is not an enticement.
- 5) Emotional distress from unwanted contact: There is a small risk that our SMS invite inadvertently reaches individuals who have passed away or do not wish to be contacted, potentially causing distress or privacy concerns. For phase 1 recruitment, EMR alerts will be checked prior to sending SMS invites. For phase 2, SA Health routinely check Births, Deaths and Marriages data each month to update their contact list, reducing the risk of causing emotional distress. It is a method they routinely use for all SMS contact with the public. To account for potential delays in reporting a child's death to the Births, Deaths, and Marriages register, a list of children and adolescents (0–18 years) who received care at WCHN and passed away in the previous month will be cross-matched with influenza and COVID-19 notifications. The PI collates a list of dates of birth for patients receiving palliative care or who have passed away. CDCB study staff cross-check this list against Influenza and COVID-19 notifications, and any matches by date of birth are excluded from receiving an SMS invitation. To minimise the risk of error, two CDCB study staff members will independently verify the age range and dates of birth identified for exclusion. SMS invitations are sent by CDCB using a secure, internally developed and managed SMS platform.
- 6) Possibility of failing to identify and manage untreated or inadequately addressed post-infectious symptoms. Refer to Appendix B: Follow-up of ongoing symptoms process.

### b. HANDLING OF WITHDRAWALS

Participants may withdraw from the project at any time and refuse to answer any survey questions. They can withdraw by contacting the study team via email or phone and indicate if they wish to withdraw all their data from the study, future contact, or just future surveys. The REDCap database will have a variable that allows the PI to add the type of withdrawal and stop future automatic surveys from being sent out. The REDCap survey will also have the option to withdraw from the study within the questionnaire.

#### c. REPLACEMENTS

Participants will not be replaced if they withdraw.

#### d. DISTRESS PROTOCOL

Refer to Appendix A

### 8. STATISTICAL METHODS

#### a. SAMPLE SIZE ESTIMATION & JUSTIFICATION

The study is primarily descriptive. At the Women's and Children's Hospital, in the last 12 months, October 2022 to October 2023, there have been 800 COVID-19 and 1,100 influenza-positive swabs.

SA Health notification of COVID-19 PCR tests in those under 18 has been 335 PCR positive in the last 3 months, with 600 notified by RAT. There will be variations in the numbers throughout the study due to changes in testing and new variants. One possible change will be that RAT results will no longer be collected. Estimated invites to be sent to SA Health notified cases are 1,340 from PCR results and 2,400 from RAT results. Year to date 9,343 influenza cases under the age of 18 have been reported (with 8,270 notified between April and October 2023)

Assuming 15% participation, based on response rates from similar studies, there would be approximately 1,222 COVID-19 cases, with 2,800 non-COVID-19 cases from SA Health notification over the 24 months of the study.

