| Number of Planned Subjects: | Assuming 15% participation, based on response rates from similar studies, there would be approximately 1,222 COVID-19 cases, with 2,800 non-COVID-19 cases from SA Health notification over the 24 months of the study.                                                                                                                                                                                                                                                                                                                                                                                                                                                                                                                                                                                                                                                                                                                                                                                                                                                                                                                                                                                                                                                                                                                                                                                                                                                                                                                                                                                                                                                                                                                                                         |

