### c. STUDY METHODOLOGY

The Vaccinology and Immunology Research Trials Unit conducts surveillance of SARS-CoV-2, and influenza infections at the Women's and Children's Hospital as part of the Paediatric Active Enhanced Disease Surveillance (PAEDS) network.

Similar to current methods used by the PAEDS network, for phase 1 of the study WCHN pathology results will be searched each fortnight by a WCHN employed level 2 Registered Nurse, and SARS-CoV-2 test-positive and influenza test-positive children and adolescents (aged 0-18 years) will be invited to participate (Figure 1).

For phase 2 of the study, SARS-CoV-2, and influenza infections will be recruited from SA Health notifications of PCR or Rapid Antigen Tests (RAT), to ensure the results are generalisable to the South Australian populations and include children and adolescents with potentially milder acute illness. Once recruitment commences through SA Health notifications, this will replace invitations sent from WCHN to avoid duplication of invitations.

COVID-19 and influenza cases parents will be sent an SMS invitation, and if they consent, agree to 1) completing a baseline survey, then surveys at 3, 6, and 12 months, 2) for the research team to review EMR if they present to a SA Health hospital (WCHN, FMC, and LMH), and permission for the study team to access the Australian Immunisation Register to check COVID-19, and influenza immunisation status.

To reimburse participants for their time and encourage the completion of surveys, a \$10 online supermarket voucher will be provided upon completion of the initial, then 3, 6, and 12-month surveys for their time (\$40 in total). If parents deem that their 12-18-year-olds are mature enough to understand the relevant information and to give consent, assent will also be collected if they wish to complete the surveys themselves. If the 12-18 year old does not agree to participate from the study, they will be withdrawn from the study.

[figure not shown]

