#### b. POWER CALCULATIONS

If the long-COVID incidence is between 1% to 6%, a sample size of 1,222 COVID cases allows for the incidence to be estimated with a precision ranging from 0.62% to 1.47%, with 20% loss to follow-up over 12 months (with precision defined as the width of a 95% CI around the estimated incidence).

**Table 2 Precision estimates based on either the proportion of long COVID in the population (between 1-6%) and the sample size ( between 550-2000)**

|             | Proportion with long COVID             |       |       |
|-------------|----------------------------------------|-------|-------|
|             | 1%                                     | 3%    | 6%    |
| Sample size | Margin of error for incidence estimate |       |       |
| 550         | 0.83%                                  | 1.42% | 1.98% |
| 1,000       | 0.62%                                  | 1.06% | 1.47% |
| 2,000       | 0.43%                                  | 0.75% | 1.04% |

Assume 360,000 population at risk (children under 18 in South Australia)

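### The planned 1,222 COVID-19 cases do not follow from the protocol's own inputs, which give 1,122, and the protocol is inconsistent on whether RAT notifications, 64% of COVID-19 invites, are a Phase 2 source

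*Protocol*

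**What the plan says.** Section 8a of the Protocol (Sample Size Estimation & Justification) reports that the COVID-19 notification count in under-18s "has been 335 PCR positive in the last 3 months, with 600 notified by RAT". It continues: "Estimated invites to be sent to SA Health notified cases are 1,340 from PCR results and 2,400 from RAT results". It then applies a participation rate ("Assuming 15% participation, based on response rates from similar studies") and concludes that "there would be approximately 1,222 COVID-19 cases, with 2,800 non-COVID-19 cases from SA Health notification over the 24 months of the study".

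The COVID-19 number recurs in the Study Synopsis under Number of Planned Subjects ("there would be approximately 1,222 COVID-19 cases"). Section 8b carries it into the precision claim: "a sample size of 1,222 COVID cases allows for the incidence to be estimated with a precision ranging from 0.62% to 1.47" per cent, allowing for 20% loss to follow-up over 12 months.

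On the Phase 2 source, section 5c (Study Methodology) says SARS-CoV-2 and influenza infections "will be recruited from SA Health notifications of PCR or Rapid Antigen Tests (RAT"). The Phase 2 paragraph of the Recruitment Procedure says: "SA Health receive notifications of SARS-CoV-2 PCR. They also receive notification of influenza PCR-positive cases". It does not mention RAT, although the Phase 1 paragraph just above it does. Section 8a adds that collection of RAT results may cease.

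**The concern.** The primary objective is an incidence estimate, so the expected number of COVID-19 participants is the only basis for its stated precision. That number appears in three places and is 100 higher than its inputs give.

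The larger exposure is the source of cases. About two-thirds of the planned COVID-19 invites are RAT notifications. The protocol is not consistent on whether these are used in Phase 2, and it foresees that they may end. It offers no expected number without them. The prediction model, the relative risk against influenza and the reinfection comparison all draw on the same PCC events.

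**Working it through.** **Inputs.** From section 8a: 335 PCR and 600 RAT notifications in 3 months, 1,340 and 2,400 estimated invites, 9,343 influenza cases in the year to date, 800 COVID-19 and 1,100 influenza swabs a year at the hospital (WCH), and 15% participation. From section 5a: 24 months of recruitment. From section 8b: 20% loss and a population of 360,000.

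**Time unit of the invites.** 335 x 4 = 1,340 and 600 x 4 = 2,400, so the invites are annual figures. This is inferred from the multiplication. If they were 24-month totals, the result would be 3,740 x 0.15 = 561, further from 1,222.

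**Expected cases = annual invites x 2 x 0.15.**
- Influenza: 9,343 x 2 x 0.15 = 2,803, which matches the stated 2,800.
- COVID-19: (1,340 + 2,400) x 2 x 0.15 = 7,480 x 0.15 = 1,122, against the stated 1,222.
- To reach 1,222 from 7,480 invites, participation would have to be 1,222 / 7,480 = 16.3%.

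**Can hospital swabs close the gap?** The missing 100 participants correspond to 100 / 0.15 = 667 invites, about 10 months of hospital swabs at 800 a year. Adding a full 12 months gives 1,122 + 800 x 0.15 = 1,242, close to 1,222. But section 8a attributes the total to SA Health notifications, and section 5c says Phase 2 replaces Phase 1 invitations. The same 12-month addition for influenza gives 2,803 + 1,100 x 0.15 = 2,968, which no longer matches 2,800. If Phase 1 instead takes up the first 3 months of the 24, the total falls: (200 + 6,545) x 0.15 = 1,012.

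**Precision.** Margin = 1.96 x sqrt[p(1 − p)/n], with the finite population correction for 360,000. At n = 1,000 this returns 0.62, 1.06 and 1.47 points for p = 1%, 3% and 6%, exactly the Table 2 row. So the stated 0.62 to 1.47 is the n = 1,000 row.

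| Enrolled | After 20% loss | Margin at 1% | Margin at 6% | Events at 1% to 6% |
|---|---|---|---|---|
| 1,222 (stated) | 978 | 0.62 | 1.49 | 10 to 59 |
| 1,122 (PCR + RAT) | 898 | 0.65 | 1.55 | 9 to 54 |
| 402 (PCR only, scenario) | 322 | 1.09 | 2.59 | 3 to 19 |

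**Role of RAT.** RAT share of invites: 2,400 / 3,740 = 64%. Without RAT for the whole period: 1,340 x 2 x 0.15 = 402, and 402 x 0.8 = 322. If RAT were lost after the first 12 months: (2,680 + 2,400) x 0.15 = 762, and 762 x 0.8 = 610, which is still within the range of Table 2.

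**The case against.** The strongest reply is that the slip hardly matters. The figure is given as approximate, the study is primarily descriptive, no test or decision rule depends on it, and the corrected post-loss number lies within the Table 2 range. Like for like, moving from 978 to 898 widens the margin by only 0.03 to about 0.06 points; part of the gap to 1.47 arises because the protocol uses the n = 1,000 row for 978. This stands.

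The 20% loss is also stated over 12 months, while the primary incidence is measured at 3 months. A loss of about 11% by month 3 would leave 1,000 of 1,122 and give exactly the stated precision. The protocol gives no 3-month loss, so one cannot say that the stated precision is out of reach. This stands too.

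The influenza check is supportive rather than conclusive, because 9,343 is a year-to-date count that is simply doubled, whereas the COVID-19 count is annualised from 3 months. The origin of 1,222 is unknown; a digit slip is plausible but is inference.

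A reader might infer that the design as written delivers only 402 cases. The documents do not support that. The Recruitment Procedure omits RAT for Phase 2 but does not exclude it, section 5c names it, section 8a budgets 2,400 RAT invites, and the inclusion criterion accepts a RAT result. Section 8a also discloses that RAT collection may end, and section 8c warns that few PCC events may limit the prediction model. What remains is an unreconciled wording and a foreseen loss of source with no number attached.

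**Conclusion.** The expected 1,222 is not supported by the inputs printed beside it; they give 1,122, a shortfall of 100 (8.2%). With the protocol's 20% loss, the precision is 0.65 to 1.55 points, against the stated 0.62 to 1.47. This is a small change and does not undermine the primary estimate.

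The inconsistency on RAT matters more, but only conditionally. If RAT were unavailable for all 24 months, about 322 children would be followed up, the margin would be about 1.1 to 2.6 points, and 3 to 19 events would be expected. At 1% incidence the normal-approximation margin is then larger than the estimate itself, although with about 3 events that approximation is poor and serves only to show scale.

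These results assume annual invites, 15% participation for both sources, constant notification rates and the 12-month loss applied at 3 months, as the protocol does. Overall severity is minor to moderate.

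**What to change.** - In the Study Synopsis and in sections 8a and 8b, restate the expected COVID-19 number as 1,122, or state the input that yields 1,222.
- Base the precision sentence in section 8b on the resulting post-loss number (about 898, hence 0.65 to 1.55 points) rather than on the n = 1,000 row.
- Reconcile section 5c with the Phase 2 paragraph of the Recruitment Procedure, so that both say whether RAT notifications are a source.
- Give the PCR-only figure (402 enrolled, about 322 after loss) as a labelled scenario beside the existing warning about RAT collection.

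The cost is wording and a line or two near Table 2, with no change to design or participant burden. The stated precision becomes slightly less favourable.
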